# Baduanjin exercise for balance function in community-dwelling older adults with cognitive frailty: a randomized controlled trial protocol

**DOI:** 10.1186/s12906-022-03764-1

**Published:** 2022-11-17

**Keywords:** Baduanjin exercise, Cognitive frailty, Randomized controlled trial, Balance function, Study protocol

## Abstract

**Background:**

Balance function provides a physiological link between the physical and cognitive function, and is a potential predictor for cognitive frailty. As a gentle mind–body exercise, Baduanjin can develop flexibility and co-ordination, thus would be is helpful for the improvement of balance function. This trial will evaluate the effect of Baduanjin on balance function in older adults with CF.

**Methods/design:**

A total of 72 community-dwelling older adults with CF will be recruited and randomly allocated (1:1) into the Baduanjin exercise group or usual physical activity control group. All participants will undergo a health education program on nutrition and diet-related knowledge for 6 sessions (30 min per session) during the intervention period. Moreover, participants in the Baduanjin exercise group will receive a 24-week Baduanjin training course of 60 min per session and 3 sessions per week, while those in the usual physical activity control group will be required to maintain their original physical activity. Primary and secondary outcomes will be measured at baseline and after the 24-week intervention period. A mixed linear model will be constructed to analyse the intervention effects.

**Discussion:**

This protocol presents an objective design of a randomized, single-blind trial that will evaluate the effectiveness and safety of traditional Chinese mind–body exercise Baduanjin training on the balance ability of community-dwelling older adults with cognitive frailty. If the results are as expected, this trial will provide evidence of the effect of Baduanjin exercise on balance in an older community-based population.

**Trial registration:**

This trial was registered in the Chinese Clinical Trial Registry with code ChiCTR2100050857 and was approved on 5 September 2021.

## Background

Cognitive frailty (CF) is an important syndrome characterized by the simultaneous presence of mild cognitive impairment and physical frailty in the absence of dementia [1]. It is reported that the prevalence of CF among older population ranges from 4.4% to 9.8% in China [2]. CF can lead to accelerated decline in cognitive and physical function, resulting in a reduction in ability of daily living and quality of life, is more predictive of poor health outcomes of older adults, such as depression, hospitalization, incapacity, dementia and even mortality in older people [3].

Balance relies on signals and feedback from the vestibular system and brain. It therefore provides a physiological link between the physical and cognitive function [4, 5]. Physical and cognitive decline in older adults with cognitive frailty could lead to progressive impairment of muscle strength and coordination, further disrupting balance function [6]. It has been reported that almost 30% of older adults with frailty suffer from balance impairment [7]. However, human balance is a complex multidimensional concept related to postural control, which is essentially the ability to maintain a posture, move between postures and not fall when reacting to an external disturbance [8]. Balance ability provides the foundation for mobility and functional independence for older adults and is an important predictor of cognitive decline and physical frailty in older adults [9, 10].

Exercise is believed to have multiple benefits on improving the balance function and physical functionality of older adults [11, 12]. Regular physical exercise in older adults is associated with increased functional independence, muscle strength, bone and joint health, and improvements in balance function [13]. Therefore, physical activity guidelines recommend that adults aged over 65 years should incorporate multicomponent physical activity to improve balance at least two days a week [14]. However, most older adults can not meet national physical activity or physical exercise recommendations due to the limitation of health and environmental conditions [15, 16]. Baduanjin is one of the most widely practised forms of traditional Chinese mind-body exercise. It consists of eight separate movements with mild to moderate exercise intensity, and is characterized by symmetrical body postures and movements, breathing control, a meditative state of mind, and mental focus, thus developing the flexibility and co-ordination of the practitioner [17]. Baduanjin exercise emphasises mind-body integration to improve both physical and mental health, so it is recommended for older persons in China [18, 19]. Studies indicate that Baduanjin has positive physiological and psychological effects for older adults with/without chronic disease, for example, improving cognitive function for older adults with or without cognitive impairment [20], alleviating cancer-related fatigue in cancer patients [21], and alleviating musculoskeletal pain in older people with chronic low back pain [22]. A recent preliminary study assessing the feasibility and efficacy of Baduanjin for prefrail/frail community-based older adults found that Baduanjin training was safe and feasible for prefrail/frail older adults with the potential to improve physical and cognitive function, reduce fall risk, improve psychological well-being, and reverse frailty status [23]. Two other studies also showed that 8-12 weeks of Baduanjin training was effective in improving balance, leg strength and mobility and was a safe and sustainable form of home-based exercise for people with chronic stroke or community-dwelling older adults [24, 25]. However, the effect of Baduanjin on balance in community-dwelling older adults with cognitive frailty requires additional investigation. The main purpose of this trial is to evaluate the effect of a 24-week Baduanjin exercise intervention on balance in community-dwelling older adults with cognitive frailty. We will investigate whether a 24-week Baduanjin exercise training protocol improves static, dynamic and overall balance ability compared with a nonspecific exercise intervention group as well as investigate the safety and feasibility of this intervention protocol. The secondary objectives are to investigate the effect of this intervention protocol on cognitive ability, physical frailty, risk of falling and muscle strength.

## Methods

This study is designed and will be conducted and reported according to the Consolidation Standards of Reporting (CONSORT) 2010 Statement regarding randomized controlled trials [26].

### Study design

This is a prospective, randomized controlled trial with blinded outcome measures comparing traditional Chinese mind–body exercise Baduanjin intervention versus nonspecific exercise intervention (maintaining usual physical activity) for community-dwelling older adults with cognitive frailty (CF). A total of 72 older adults with CF will be randomly (1:1) allocated into the Baduanjin intervention group (60 min per session, three sessions per week for 24 weeks) and the control group (maintaining their original usual physical activity). The study procedure and outcome assessment schedule for this trial are presented in Figs. 1 and 2. This trial was registered prospectively at Chictr.org.cn with registration number ChiCTR2100050857 on 5 September 2021.

**Fig. 1 Fig1:**
[figure not shown]
Flow chart of the trial

**Fig. 2 Fig2:**
[figure not shown]
Schedule of enrolment, assessments and interventions. The × indicates at which point of the trial the respective assessments will take place. SLST: Single-leg stance test; TUGT: Timed Up and Go test; FRT: Functional reach test; Tinetti POMA: Tinetti Gait and Balance Scale; mini-BES Test: Mini Balance Evaluation System Test; MoCA: Montreal Cognitive Assessment Scale; EFS: Edmonton Frailty Scale; MFES: Modified Fall Efficacy Scale; CST: the 30-s chair-stand test

## Sample size calculation

Sample size was calculated based on the group mean comparison formula by using the effect size of the primary outcome (mini-BESTest scores) from the study conducted by Ni M et al. [27]. Considering 80% efficacy and 5% I type error (two tails), at least 30 subjects in each group were enough to detect the target effect mini-BESTest changes between two groups. Considering a 20% dropout rate, 36 subjects each group are planned to be recruited in this trial. Calculations were performed using Gpower 0.3.1.6.2 software.

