### Recruitment

Eligible older adults will be recruited from three community centres (Xingshengli, Huashengli, Zhongjinhaitangwan) in Pudong New District in Shanghai city in China. The potential participants can obtain specific recruitment information through a combination of online and offline way, including the community health service centre, community health management system, community health lectures, WeChat and the internet. They will be first assessed for eligibility by two research assistants according to the inclusion and exclusion criteria, and then the informed consent will be discussed if they are interested in this trial. After voluntarily signing the informed consent form, he or she will be invited to participate in the trial. Recruitment starts on 1 March 2021 and end when 72 participants are enrolled.

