### Trial status

At the time of submission, recruitment for the trial has been completed. The first participant was included on 30 December 2021.

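### 36 per group does not keep the stated minimum of 30 completers at the stated 20% dropout; it covers at most 16.7%

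*Protocol article*

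**What the plan says.** In the protocol article, under Sample size calculation, the size rests on a comparison of two group means, "by using the effect size of the primary outcome (mini-BESTest scores") taken from a cited study. The stated targets are "Considering 80% efficacy", which from its context means power, and "5% I type error (two tails"). The result is that "at least 30 subjects in each group were enough to detect the target effect mini-BESTest changes between two groups". The next step is the dropout allowance: "Considering a 20% dropout rate, 36 subjects each group are planned to be recruited in this trial".

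The rest of the article agrees with 36 per group. Study design says "A total of 72 older adults with CF will be randomly (1:1) allocated", and Recruitment is to "end when 72 participants are enrolled". The abstract gives the same total. Trial status reports that "recruitment for the trial has been completed". The article writes out no inflation formula, adds no allowance elsewhere, and gives no second meaning of dropout.

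**The concern.** An allowance for dropout has one purpose: the number left after the assumed loss should still meet the requirement. Here it does not. The requirement (30), the loss (20%) and the recruitment target (36) are stated together, and the third does not follow from the first two.

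At stake is what a reader takes from the statement. As written, it says that 72 participants protect the 80% power target against a loss of one in five. The margin is narrower than that. It matters somewhat in a 24-week exercise programme whose authors, in the Discussion, name adherence as a limitation.

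**Working it through.** **Inputs from the Sample size calculation section.** Required number per group n = 30; dropout 20%; planned number per group 36; power 80%; two-sided 5%. The effect size and SD are not given as numbers.

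**Reproducing the planned figure.** Multiplying up gives 30 x (1 + 0.20) = 36, an exact match. That this was the method is an inference, because no formula is shown.

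**Checking what remains.**
- Completers at 20% loss: 36 x (1 - 0.20) = 28.8 per group, or 57.6 in total, against 30 and 60.
- Number needed to keep 30: 30/(1 - 0.20) = 37.5, so 38 per group and 76 in total. Check: 38 x 0.80 = 30.4.
- Largest loss that 36 can bear: 1 - 30/36 = 16.7%, which is 6 per group.

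These three results need no assumption beyond the article's own figures, and they hold whichever formula was used.

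**How likely the shortfall is.** Assume that each participant drops out independently with probability 0.20. The chance that a given arm of 36 keeps 30 or more is 0.401, so it falls below 30 with probability 1 - 0.401 = 0.60. Both arms keep 30 with probability 0.401 x 0.401 = 0.161, so at least one falls short with probability about 0.84.

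**Consequence for power (assumption needed).** Assume that 30 is the smallest number per group reaching 80% in a two-sample t-test (noncentral t, 2n - 2 degrees of freedom, noncentrality d x sqrt(n/2)). Exactly 80% at n = 30 gives d = 0.736. Exactly 80% at n = 29 gives d = 0.749, so d lies between these values.

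| Remaining per group | Power at d = 0.736 | Power at d = 0.749 |
|---|---|---|
| 28 | 77.1% | 78.6% |
| 28.8 (expected) | 78.3% | 79.7% |
| 29 | 78.6% | 80.0% |
| 30 | 80.0% | 81.4% |

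The normal approximation gives nearly the same low end: d = 0.723, with 77.2% at 28, 78.4% at 28.8 and 78.7% at 29. The effect detectable with 80% power rises from 0.736 SD at 30 per group to 0.751 SD at 28.8.

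**The case against.** The strongest objection is that the shortfall hardly matters. It is 2 per group, the loss of power runs from almost nothing to about 3 points, and recruitment is over. That is right about the size and limits what should be asked for. It does not make the stated allowance correct.

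A second objection is that the analysis is by intention to treat with multiple imputation, so all 72 stay in. They stay in the analysis set, but their unobserved 24-week outcomes are not recovered. Outcome measures places assessments only at baseline and after the intervention, so a participant who drops out has no intermediate value to inform the imputation. The sample size section itself treats dropouts as a loss to be made good.

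A third objection is that the planned mixed model, which uses the baseline value, may have different power from a simple comparison of means. This stands as a limit on the power figures: they describe a t-test on completers, and the model's power depends on a baseline-to-follow-up correlation that the article does not give. The headcount conflict is untouched, because the size was derived from a comparison of means and no gain from the model is claimed.

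A reader might also infer more than the article supports: that power definitely falls below 80%, or that it is 78%. Neither can be said without the effect size. If 30 was rounded up slightly, an effect of 0.751, just above the range used here, would still give 80% at 28.8 per group.

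**Conclusion.** The point holds as a conflict of stated numbers. With 20% dropout, 36 per group leaves 28.8, which is short of the stated minimum of 30. The correct inflation is 38 per group (76 in total), and the planned size covers dropout of at most 16.7%. This part is certain on the article's own figures.

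The loss of power is small and conditional. If 30 is the smallest adequate number for a two-sample t-test, power at 20% dropout is about 78.3% to 79.7% at the expected 28.8 per group, with 77.1% to 78.6% if 28 remain and 78.6% to 80.0% if 29 remain. The article does not support calling the trial seriously underpowered, giving one power figure as fact, or stating as known that the authors multiplied by 1.2.

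**What to change.** Restate the figures and do not enrol more. Suggested text: 72 participants (36 per group) retain 30 per group for up to 16.7% dropout; at 20% dropout about 28 to 29 per group remain. Then add the standardised effect that was entered in the sample size software, and the power at that remaining number recomputed from it. A figure such as 78% should not be inserted in its place, since it would only be worked back from 30 and not from the effect actually used.

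The cost is one corrected sentence and one recalculation from an input that the authors should already hold. Conduct and analysis do not change. The stated margin becomes slightly less favourable, and the base figure of 30 becomes reproducible.

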## Study population

### Eligibility criteria

Inclusion criteria: (1) community-dwelling older adults aged over 60 years; (2) meet the CF criteria [28]; (3) no regular physical exercise within half a year (regular exercise defined as a frequency of at least 20 min at least twice a week); (4) written informed consent.

Exclusion criteria**:** (1) those suffering from uncontrollable blood pressure (systolic blood pressure ≥ 160 mmHg or diastolic blood pressure ≥ 100 mmHg); (2) with alcohol or drug abuse; (3) with exercise contraindications such as mental illness, depression, coronary artery disease, musculoskeletal disorders, etc.; (4) joining other trial.

### Recruitment

Eligible older adults will be recruited from three community centres (Xingshengli, Huashengli, Zhongjinhaitangwan) in Pudong New District in Shanghai city in China. The potential participants can obtain specific recruitment information through a combination of online and offline way, including the community health service centre, community health management system, community health lectures, WeChat and the internet. They will be first assessed for eligibility by two research assistants according to the inclusion and exclusion criteria, and then the informed consent will be discussed if they are interested in this trial. After voluntarily signing the informed consent form, he or she will be invited to participate in the trial. Recruitment starts on 1 March 2021 and end when 72 participants are enrolled.

### Baseline assessment

Baseline information of all eligible participants will be collected by the recruiters using a self-designed questionnaire. Baseline information includes the participants’ personal general data and demographic information, such as gender, age, height, weight, years of education, marital status, occupation, medical history, lifestyle, diet, and physical activity.

### Randomization, allocation concealment, and blinding

The programs of randomization and allocation concealment will be performed as reported in our previous trail protocol [29]. Although it is difficult to blind the participants in this trial, the outcome assessors and statisticians will be blinded according to the program described in our previous trial protocol [29].

## Intervention protocol

All participants will participate in a health education program on nutrition and diet-related knowledge of cognitive frailty, which will consist of lectures (30 min per session once every 4 weeks) and knowledge booklets (every 4 weeks) during the intervention period.

### Control group

Participants in the control group will not receive any specific exercise training (i.e., maintain their original usual physical activity).

### Baduanjin exercise training group

Participants in the Baduanjin exercise training group will receive Baduanjin exercise training with a frequency of 3 days a week and 60 min a day for 24 weeks. Baduanjin practice will be conducted at three community centres (Xingshengli, Huashengli and Zhongjinhaitangwan) with 10–15 individuals per centre. Three professional teachers who have been occupied in the Baduanjin teaching at the Shanghai University of Medicine & Health Sciences (SUMHS) for at least 5 years will be employed to teach participants’ Baduanjin practice. The training scheme of Baduanjin exercise is planned as described in detail previously [29].

## Outcome measures

In this trial, the primary and secondary outcomes will be measured at baseline (1–2 weeks before randomization) and at the end of the 24-week intervention period (25 weeks after randomization). All outcome assessments will be independently conducted by experienced and blinded assessors. A summary of all measurements in this trial is shown in Fig. 2.

### Primary outcome measure

The primary outcome is balance ability measured using the Tinetti Performance-Oriented Mobility Assessment (Tinetti POMA) and the Mini Balance Evaluation System Test (Mini-BESTest).

The Tinetti POMA scale contains both a balance and a gait component. The balance component of the test assesses the individual’s ability to maintain postural control, and the gait component assesses the symmetry, continuity, path, base of support, and postural sway during gait [30]. The Tinetti POMA has been widely used to screen balance and gait abnormalities in the community or clinical population, with well-demonstrated reliability and validity [31]. The Mini-BESTest includes four sections, anticipatory postural adjustments (APA), reactive postural control (RPC), sensory orientation (SO) and dynamic gait (DG), and consists of 14 items that examine performance tasks related to dynamic balance, obstacle negotiation, reactions to external forces, and performance during dual tasking with cognitive challenge [32].

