## Statistical analysis

Data will be analysed according to the intention-to-treat principle (ITT) using the SPSS 21.0 software package by an independent statistician, with a statistical significance of *p* < 0.05 on both sides. Missing data will be complemented using the multiple imputation method.

Descriptive statistics will be performed using the mean and standard deviation (SD)/median and interquartile ranges for continuous outcomes or percentages for categorical outcomes. Baseline characteristics will be compared between the Baduanjin exercise training group and the control group to identify the adequacy of randomization and possible confounders. We plan to analyze primary and secondary outcomes using the mixed-effect linear model with restricted maximum likelihood, and group (Baduanjin exercise training and the control group), time (baseline and after intervention) and possible confounding factors will be introduced into the model as independent variables.

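### The outcome section makes two scales primary but the sample size rests on Mini-BESTest alone, so the stated 5% error and 80% power do not both carry over to the primary outcome as written

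*Protocol article*

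**What the plan says.** Two sections of the protocol article identify the primary outcome differently.

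- Primary outcome measure, which gives this definition: "The primary outcome is balance ability measured using the Tinetti Performance-Oriented Mobility Assessment (Tinetti POMA) and the Mini Balance Evaluation System Test (Mini-BESTest". Two instruments are named and no combined score is defined.
- Sample size calculation: the trial is sized "by using the effect size of the primary outcome (mini-BESTest scores", so here the primary outcome is one scale. The operating characteristics are given as "Considering 80% efficacy and 5% I type error (two tails", with the result that "at least 30 subjects in each group were enough to detect the target effect mini-BESTest changes between two groups". Allowing for 20% dropout, 36 per group are to be recruited.
- Statistical analysis: the only threshold is general, "with a statistical significance of *p* < 0.05 on both sides". One model type serves every outcome: "We plan to analyze primary and secondary outcomes using the mixed-effect linear model with restricted maximum likelihood".

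No section gives an effect size, variance or power for Tinetti POMA, or says what pattern of results on the two scales counts as success.

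**The concern.** The 5% and the 80% were set for one test of one scale, but the primary outcome as defined involves two. With two scales, the error rate and power of the main claim depend on the rule that combines them. If that rule stays open until results are known, the favourable scale could be put forward as the primary finding, with a false-positive rate above the one advertised. If the rule turns out to be that both must succeed, the trial is smaller than its stated power requires. Under Trial status, recruitment was already complete at submission, so enlarging the sample is no longer an easy remedy.

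**Working it through.** **Inputs from the document:** two-sided alpha 0.05, power 80%, 30 evaluable per group, 36 per group recruited, 1:1 allocation.

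**Assumptions, because the document gives no figure:** the Mini-BESTest effect size (solved backwards below); the Tinetti POMA effect (set equal to that of Mini-BESTest, then to 75% of it); and the correlation between the two test statistics (0 to 0.9).

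**The plan's own figure.** The 30 per group cannot be reproduced forwards without the effect size. Solving backwards with the normal approximation:

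d = (z₀.₉₇₅ + z₀.₈₀)/√(n/2) = (1.960 + 0.842)/√15 = 0.723.

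The noncentral t version gives d = 0.736. The 36 follows as 30 × 1.2.

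**Rule A: either scale suffices, each at 0.05.** For independent scales, error = 1 − 0.95² = 9.75% and power for at least one win = 1 − 0.20² = 96%. Correlated values come from the bivariate normal distribution. Power cannot fall below 80% under this rule, because Mini-BESTest alone supplies that.

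**Rule B: both scales required, each at 0.05.** The error stays at or below 5%. For independent scales with equal effects, power = 0.80 × 0.80 = 64%. If the POMA effect is 75% of the Mini-BESTest effect, power on POMA alone is 56%.

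| Correlation | A: error | A: power, at least one | B: power, equal effects | B: power, POMA effect 75% |
|---|---|---|---|---|
| 0 | 9.75% | 96% | 64% | 45% |
| 0.5 | 9.1% | 91% | 69% | 50% |
| 0.7 | 8.3% | 89% | 71% | 53% |
| 0.8 | 7.8% | 87% | 73% | 54% |
| 0.9 | 7.0% | 85% | 75% | 55% |

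**Rule C: 0.025 per scale.** The error is at or below 5%. Power on Mini-BESTest at 30 per group, by the normal approximation, is Φ(2.802 − 2.241) = Φ(0.560) = 71.2%; the noncentral t gives 70.7%.

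**Rule D: Mini-BESTest as the only primary.** One test at 0.05 with 30 per group keeps the stated 5% and 80%.

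**Size needed to restore 80%.** Rule C, for Mini-BESTest: n = 2(2.241 + 0.842)²/0.723² = 36.3, so 37 per group, or 47 after dividing by 0.8 for dropout. Rule B with equal effects: 40, 38 and 36 per group at correlations 0, 0.5 and 0.8, or 50, 48 and 45 after dropout. The plan has 30 evaluable and 36 recruited.

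**The case against.** **An analysis plan that is not shown may set a multiplicity rule, and a journal article condenses a fuller protocol.** This stands to the extent that the missing alpha rule is not itself an error. It does not remove the disagreement between two printed sections about what the primary outcome is.

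**Balance ability is one construct.** That may be so clinically, but the outcome section names two instruments without a combined score, and the sample size section treats one of them as the primary outcome.

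**A reader might infer that neither the 5% nor the 80% holds.** The documents do not support that. Under Rule A the error rises but power is at least 80%. Under Rules B and C the error holds and power falls. No single rule breaks both.

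**A reader might infer that the plan tests each scale at 0.05 and accepts whichever wins.** That is the natural reading of a general threshold, but it remains an inference. The text sets no level per scale and no success rule.

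**A reader might add that the Background's main question, whether training "improves static, dynamic and overall balance ability", promotes secondary outcomes to primary.** This does not hold as a contradiction. An objective may be wider than its endpoint, the static and dynamic tests are listed explicitly as secondary, and Mini-BESTest is itself described as covering dynamic balance.

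**A split alpha with success on either scale might keep both figures.** With equal effects at 30 per group, power for at least one win at 0.025 each is 92% at correlation 0, 82% at 0.7, 79.9% at 0.8 and 77% at 0.9. It falls towards the 71% for Mini-BESTest alone as the POMA effect shrinks. Such a rule could be defended, but the protocol states neither the rule nor any POMA effect to support it.

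**Conclusion.** The point holds as an internal contradiction: the outcome section has two primary scales and the sample size section has one. The stated 5%, and the stated 80% as derived for Mini-BESTest, do not both carry over to a two-scale primary. Which of them gives way depends on a rule the document leaves open: error of 7.0% to 9.75% if either scale suffices without adjustment, power of 64% to 75% if both are required, or about 71% power on Mini-BESTest with 0.025 each.

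The contradiction can be read directly from the text. The sizes are illustrative. They rest on an effect of about 0.72 to 0.74 solved from 30 per group, on assumed correlations, and, for the both-required figures, on an equal standardized effect for POMA. A POMA effect of 75% lowers that power to 45% to 55%. Only with Mini-BESTest as the sole primary do both stated figures stand at the planned size.

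**What to change.** By a dated amendment made before unblinding, name the Mini-BESTest total score at the post-intervention assessment as the single primary outcome, tested at two-sided 0.05 to match the sample size. Make Tinetti POMA the first key secondary outcome, tested confirmatorily only if Mini-BESTest is significant. Use the same definition in the outcome, sample size and analysis sections.

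If both scales are to remain primary, state whether either or both must succeed and at what alpha. State the POMA effect and correlation assumed, and restate the power for the number enrolled.

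The recommended change needs no extra participants, but it is more than an edit of wording. POMA alone could no longer carry the primary claim, and a published primary outcome would be changed after enrolment. The amendment and the final report should therefore give the reason and show that the change preceded unblinding.
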